##### Cognitive remediation

MyBrainTraining^©^ (BBG Entertainment GmbH) [76] is a newly developed computer-based cognitive remediation program, which aims to improve cognitive functioning deficits present in schizophrenia by presenting a series of cognitive exercises, which are repeatedly practiced. In the present study, participants complete all exercises independently. The program consists of thirty exercises aimed at training executive functioning through different types of tasks, including those of vision, arithmetic, logic and memory. All exercises are conducted on PC’s over the Internet. The exercises were designed during the development of the “Train your Brain with [name]” program in cooperation with the Industry University Research Project and [name]. [name].

Based on the participant’s performances, the difficulty of each task automatically increases or decreases. The exercises are similar to video games and include fun or motivational elements. The administrator has the ability to determine specific training plans and to adapt exercises to each patient’s needs (e.g., level of difficulty, varied time limits, etc.). Data protection and security comply with industry standards.

For the present study, participants are asked to complete the exercises in a specific order and are provided with feedback from the program on their performance, which they record on an exercise log. Log-in information is not shared with participants to prevent practice at home. Like the MCT+ group, three months after the final session participants are sent a postcard asking if they are still using the skills learned while completing MyBrainTraining^©^ and if they have continued cognitive exercises using other modalities (e.g., crossword puzzles, Sudoku, etc.).

#### Sample size

This is the first trial of MCT+ in which participants are followed for a longer period after completion of treatment. As such, determination of optimal sample size was based on an initial trial of MCT+ [34], which included 48 patients and yielded medium to large effect sizes (ɳ_partial_^2^ = .08 – .13) compared to cognitive remediation (CogPack^©^). In this pilot study, non-compliance rates were low over the 4-week follow-up (4 %) and patients’ acceptance was excellent. Most patients eligible for treatment agreed to participate in the study, although 26 % refused participation. Non-completion rate from a 6-month follow-up of group MCT was 14 % after six months, although the greatest number of participants (10 %) dropped out during the first four weeks of the study (from baseline to the post-treatment follow-up). Based on this previous work, we anticipate a completion rate of 80 % for the primary endpoint (T0-T2). See Fig. 1 for a flow chart of the recruitment and study procedure.

**Fig. 1 Fig1:**
[figure not shown]
Study flow

Using calculation software PASS 2008 [77] with a conventional alpha level of .05 and a beta-value of .20 for a two-tailed test, it was calculated that each group must be comprised of 130 patients to detect a small to medium effect (*d* = 0.35) at the 6-month follow-up testing. Assuming a dropout rate of 20 % (including dropout due to non-compliance and loss to follow-up), the study will be conducted with a sample size of 328 patients or 82 patients per trial center.

#### Statistical analyses

Two sets of statistical analyses will be performed. First, on an intention-to-treat (ITT) basis, which considers all patients with available baseline data. An expectation maximization (EM) algorithm will be used to estimate missing values. The second set of analyses will include only participants with baseline and post and/or follow-up data (per protocol, PP). An ANCOVA model will be conducted with group (MCT+/MyBrainTraining^©^) difference between T0 and T1 as the dependent variable. Both treatment (independent of time) and condition*time interaction effects will be evaluated. Change scores between T0 and T2 for the primary outcome, as well as analyses over both time points (T0 vs. T1 and T0 vs. T2) for secondary endpoints (PANSS syndrome scores, Fish Task, PHQ-9, CDSS, NSA, WHOQOL-BREF, RSE, BCIS, PSP, neuropsychological outcomes), will be tested using analogous models. Baseline performance or symptoms, antipsychotic drugs (% of maximum dosage) and concurrent treatment (e.g., group MCT, individual psychotherapy, and occupational therapy) will be included in the models as covariates to explore possible impacts on treatment outcome. Secondary analyses will be conducted to examine change between T1 vs. T2 for primary and secondary outcomes.

A logistic regression will be used to analyze variables that may identify participant response to MCT+, including severity of baseline psychotic symptoms, level of motivation for treatment, satisfaction with group assignment, baseline depression, and number of sessions completed. Two groups will be defined (criterion: decline of 25 % or more points on the PSYRATS from T0 to T2) and non-responders. No interim analyses will be conducted. In a sensitivity analysis, we will explore the effect of missing values using various imputation methods (best and worst observation carried forward, last observation carried forward, full-informational maximum likelihood).

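### The main ITT analysis reads as a single EM fill of missing scores followed by ordinary ANCOVA, which understates the standard error if arm is in the EM step and shrinks the effect if it is not

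*Protocol article*

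**What the plan says.** The Statistical analyses section plans two analysis sets. The first, intention-to-treat, takes every patient with baseline data; for it, "An expectation maximization (EM) algorithm will be used to estimate missing values". The second, labelled per protocol, keeps participants with baseline plus post and/or follow-up data. The model is an ANCOVA on change from T0 to T1, with an analogous model for T0 to T2. A sensitivity analysis will explore other ways of handling missing values: "best and worst observation carried forward, last observation carried forward, full-informational maximum likelihood".

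The Sample size section expects 80% completion for the T0-T2 endpoint. It plans for 20% dropout, "including dropout due to non-compliance and loss to follow-up".

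**The concern.** EM estimates of missing values are conditional means: they lie on the fitted regression surface with no residual scatter. If they are put into ANCOVA as data, each counts as a full observation but adds nothing to the residual variance. At 20% missing this applies to 328 × 0.20 = 65.6, about 66 scores at T2.

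Two different errors can follow, depending on a detail the article does not give.

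- **Arm in the EM step.** The effect estimate is unbiased, but the standard error is too small and the test rejects too often.
- **Arm not in the EM step.** The filled values carry little or no arm difference of their own, so the estimate is pulled towards zero.

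At stake is either the false-positive rate of the main ITT test or the size of the effect it reports.

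**Working it through.** **1. The plan's own sample size.** Inputs from the Sample size section: "with a conventional alpha level of .05 and a beta-value of .20 for a two-tailed test", and "to detect a small to medium effect (*d* = 0.35) at the 6-month follow-up testing".

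- n per group = 2 × (1.960 + 0.842)² / 0.35², which rounds up to 129. The t-test solution is 129.1, rounded up to 130. This agrees with the article: "it was calculated that each group must be comprised of 130 patients".
- Inflation for dropout: 260 / 0.80 = 325, against the planned 328 = 4 × 82.
- With 328 × 0.80 = 262 observed, or 131 per arm, power for d = 0.35 is 80.9%. Counting all 164 per arm as observed would suggest 88.7%.

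The planned size is therefore right for an analysis of observed outcomes.

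**2. Arm in the EM step, by formula.** Let m be the missing fraction, σ² the residual variance and N the total.

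- Reported variance of the effect ≈ 4 × (1 − m)σ² / N, because filled values have zero residual but N is counted in full.
- True variance ≈ 4σ² / [(1 − m)N].
- Reported SE / true SE ≈ 1 − m.
- Actual two-sided alpha = 2 × [1 − Φ(1.96 × (1 − m))].

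| m | Where the figure comes from | SE ratio | Actual alpha |
|---|---|---|---|
| 20% | planned dropout | 0.80 | 11.7% |
| 14% | six-month loss in the earlier group MCT study | 0.86 | 9.2% |
| 10% | loss in the first four weeks of that study | 0.90 | 7.8% |

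**3. Arm left out, by formula.** If the filled values carry no arm difference, the estimate is about (1 − m) × 0.35 = 0.80 × 0.35 = 0.28. Its sampling SD shrinks by the same factor and then matches the reported SE, so the test keeps its level.

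**4. Simulation.** The settings below used N = 328, 20% missing at T2 completely at random, EM fill, then ANCOVA with baseline as covariate. With that covariate, the arm coefficient is the same for the T2 score as for change from T0. The correlations, the pattern of missing T1 scores and 1:1 allocation are assumptions.

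| Setting | Arm in EM: SE ratio | Arm in EM: type I error | Arm out: type I error | Arm out: estimate of 0.35 |
|---|---|---|---|---|
| All correlations 0.5 or 0.7; 70% or 100% of those missing T2 also miss T1 | 0.78–0.83 | 10–13% | 4.5–5.5% | 0.28–0.29 |
| Correlations 0.6 (T0–T1), 0.5 (T0–T2), 0.7 (T1–T2); 10% missing at T1 | 0.83–0.85 | 9.5–9.7% | 5.0–5.1% | 0.30 |

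The first row used 1,500 simulated trials per cell, so the simulation error of a 10% rate is √(0.10 × 0.90 / 1500), about 0.8 percentage points. In that row, ANCOVA on observed T2 scores only gave an estimate of about 0.35 and type I error of 4.2 to 6.1%.

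**5. Adding random residuals to a single fill.** With arm in the model and correlation 0.5, the SE ratio is still 0.85 and type I error 9.4%. One filled data set is not enough, with or without added noise.

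**6. The carried-forward sensitivity analyses.** In the second setting, last observation carried forward gave SE ratios of 0.99 to 1.01 and type I error of 4.8 to 5.8%. Best and worst observation carried forward gave SE ratios of 1.01 and type I error of 5.1% and 4.7%. Their weakness is bias: last observation carried forward estimated 0.35 as 0.31.

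**The case against.** The article never says that values are filled once or analysed as observed, and it is a condensed account whose analysis plan is not shown. Details of the imputation model may properly sit in that plan. This is fair, and the reading is an inference. It is still the natural one: EM is said to estimate values rather than parameters, the ITT set can be kept whole in an ANCOVA only if gaps are filled, and the direct likelihood method is listed separately as a sensitivity analysis.

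A reader might infer that the main p-value is bound to be wrong. The documents do not support that, because inflation occurs only if arm is in the EM step. If arm is left out, the test holds its level and the error is attenuation, which is conservative for a superiority claim.

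A reader might also infer that the carried-forward analyses repeat the standard-error defect because they too are single fills. They do not: each carries a patient's own observed score, and their standard errors came out correct in simulation.

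Finally, other planned analyses could expose the problem. The full-information likelihood analysis is valid under missing at random. The second analysis set, if run on observed T2 scores, comes close to a sound complete-case check (estimate 0.349, type I error 5.3% under the assumed setting). That set, however, also admits patients with T1 but no T2. Both analyses can show a discrepancy; neither replaces the main ITT result.

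**Conclusion.** The point holds in a conditional form. As the article reads, the main ITT analysis has one of two defects, and it does not say which. With arm in the EM step, the standard error is about 0.78 to 0.85 of its true value and type I error about 9.5 to 13% at 20% missing. With arm left out, type I error is near 5% but an effect of 0.35 SD is reported as about 0.28 to 0.30.

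The standard-error result depends mainly on the missing fraction. The rest assumes dropout completely at random, 1:1 allocation and the correlations listed above. A full 20% of missing scores is the upper end of the planning figures, since that rate includes non-compliance and some non-compliers may still be assessed. Loss is also likely to be lower at T1, the time point in the stated primary research question. The defect shrinks with less missing data but does not vanish: alpha is still 7.8% at 10% missing with arm in the EM step.

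The planned sample size stands and should not be questioned on this ground.

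**What to change.** Replace single EM filling as the main ITT analysis with one of these:

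- the full-information maximum likelihood analysis the article already names, or a repeated-measures mixed model with baseline, arm, visit and arm-by-visit, fitted to all observed data; or
- multiple imputation with arm and the T1 score in the imputation model, combined by Rubin's rules.

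The cost is revised wording and some programming. The confidence interval will be wider than the one EM filling would report, by a factor of up to about 1/0.80 = 1.25 at 20% missing or 1/0.90 = 1.11 at 10%, but it will be correct. No more patients are needed. The article reports that recruitment was still under way, so the change could be made before analysis.

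Replacing the carried-forward analyses with delta-adjusted imputation, to examine data missing not at random, is optional and not part of correcting this error.

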**Table 2 Tab2:** List 1 of study measures and questionnaires

Instrument	Baseline	6 weeks (post)	6 months (follow-up)
*Diagnostic and Measures of Psychopathology*			
Sociodemographic interview	X	X	X
Mini Neuropsychiatric Interview	X		X
Positive and Negative Syndrome Scale	X	X	X
Psychotic Symptom Rating Scales	X	X	X
Calgary Depression Rating Scale	X	X	X
Personal and Social Performance Scale	X	X	X
Negative Symptom Assessment – 4	X	X	X
*Neurocognitive Measures*			
Trail Making Test A & B	X	X	X
Test d2	X	X	X
German Vocabulary Test (premorbid intelligence)	X		
Rivermead Behavioural Memory Test, Story Recall	X	X	X
*Cognitive biases*			
Fish Test	X	X	X
*Questionnaires*			
Short Form-12	X	X	X
Patient Health Questionnaire	X	X	X
Beck Cognitive Insight Scale	X	X	X
Rosenberg Self-Esteem Scale	X	X	X
Evaluation of the Intervention		X	X

A measure was developed by the authors (BS, FB, SM) to assess therapist adherence to the MCT+ manual. For patients who provide informed consent, therapy sessions are video recorded and psychologists familiar with MCT+ assess adherence. Additionally, questionnaires developed by the authors (SM) assessing participants’ acceptance of both interventions are completed after every training session attended.

Participants are allowed to use antipsychotic medications during the entire study and are not withheld from other psychosocial treatments they might be offered or are currently participating in, including participation in MCT group therapy. Participation in concurrent interventions is recorded at post- and follow-up testing sessions. Participants are allowed to withdraw from intervention or assessment sessions upon request without having to disclose a reason. All participants are compensated with 30€ upon completing of each assessment session.

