#### Intervention

To ensure comparability of results, both interventions are implemented for the same duration (6 weeks; 12 sessions) and frequency (45–60 min per session). Psychologists undergoing post-graduate training provide both MCT+ and computerized CR. All MCT+ trainers completed a 2-day MCT+ workshop and receive regular intervision from two of the authors of the MCT+ therapy program (RV, FB).

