11. Dealing with the Diagnosis and Relapse Prevention	Based on information gained throughout the 6 weeks, patients are given information about their disorder and how to cope with the diagnosis in everyday life, especially regarding communication of information about the disorder in social situations. Patients are made aware of possible ways the disorder may progress. It can also be beneficial to involve relatives in this final session because they often recognize prodromal symptoms earlier on than patients.	An emergency plan is created in cooperation with the patient, which clarifies whom the patient should seek in case of a crisis (e.g., an institution that the patient trusts, a therapist). Stress reducing and coping strategies are discussed. It is also discussed with the patient in which situations revealing their diagnosis may be helpful or unhelpful.

Although the MCT+ units are presented in the order provided in Table 3, it is emphasized that treatment should be tailored to the individual needs and insight level of the patient, as well as trainer preferences. As such, more time can be spent on any one unit and themes can be skipped completely. For the purposes of the RCT, all trainers were instructed to complete the first therapy units focused on discussion of the importance of trust and openness to the therapeutic relationship and taking a case history (Therapy Unit 1), introducing MCT+ (Therapy Unit 2) and developing a personal illness model (Therapy Unit 3; when appropriate, this unit can also be completed at a later stage during therapy). In addition, trainers are to choose at least two units addressing cognitive biases. There are also two units devoted to affective problems (Therapy Unit 9: Depression and Thinking; Therapy Unit 10: Self-Esteem). In the last unit, focus is on coping with (the stigma of) illness, preparing patients for the discontinuation of therapy and discussing relapse prevention strategies (Therapy Unit 11). Each unit includes a number of therapy demonstrations, as well as worksheets displaying discussion topics and exercises that serve to illustrate the main topic. Certain exercises (e.g., card trick in Therapy Unit 4) are preferably presented with the help of a computer laptop or tablet.

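### The set labelled 'per protocol' is defined by having outcome data, not by treatment received, so agreement with ITT says nothing about non-adherence

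*Protocol article*

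**What the plan says.** The Statistical analyses section describes two analysis sets. The first is given as "First, on an intention-to-treat (ITT) basis, which considers all patients with available baseline data", and the next sentence assigns an EM algorithm to missing values. The other is defined in one sentence, as "only participants with baseline and post and/or follow-up data (per protocol, PP". No other section gives a different per-protocol definition.

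Three further statements bear on this:

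- Procedure and treatment allocation: "Participants are allowed to withdraw from intervention or assessment sessions upon request without having to disclose a reason".
- Intervention: "both interventions are implemented for the same duration (6 weeks; 12 sessions", so the planned exposure is stated and is the same in both arms.
- Statistical analyses, in the logistic regression of response to MCT+: the candidate predictors include "baseline depression, and number of sessions completed". This is the only analysis in which sessions attended play a part.

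**The concern.** A per-protocol analysis is normally read as the comparison among patients who received treatment broadly as planned. Set beside ITT, it shows whether the conclusion depends on patients who did not take up the intervention. The set described here cannot do that, because membership depends on attending an assessment and not on attending treatment.

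What is at stake is interpretation. If the ITT and 'PP' results agree, the label invites the conclusion that non-adherence made no difference, when the pair has compared only two ways of dealing with missing outcomes. If they disagree, the label points to adherence when the cause lies in the missing data. The article makes incomplete exposure a realistic prospect: its Discussion cites average attendance of 80 % of MCT+ sessions in the earlier trial.

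**Working it through.** The point turns on a definition, so the main check is to apply the stated rules to each kind of patient.

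**The plan's own figure, for reference.** Inputs from the Sample size section: d = 0.35, two-sided alpha 0.05, power 0.80, 20 % dropout.

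- Per group: n = 2(z₀.₉₇₅ + z₀.₈₀)² / d² = 2(1.960 + 0.842)² / 0.35² = 15.70 / 0.1225 = 128.2, so 129. The t-test version gives 129.1, so 130, as stated.
- Total: 260 / 0.80 = 325. The plan has 4 × 82 = 328, consistent with rounding up to equal centres.

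The sample size reproduces, and nothing in it depends on how the second analysis set is labelled.

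**Who falls in which set.** All patients below have baseline data.

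| Patient | ITT | 'PP' as written | Treated as planned |
|---|---|---|---|
| Attended treatment; assessed at T1 and/or T2 | yes | yes | yes |
| Left the intervention early; assessed at T1 and/or T2 | yes | yes | no |
| Attended treatment; no T1 and no T2 | yes | no | yes |
| Left the intervention early; no T1 and no T2 | yes | no | no |

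1. The second row can occur because withdrawal from the intervention and withdrawal from assessment are allowed separately. These are the assessed non-compliers, and the definition keeps them.
2. The 'PP' column follows the assessment status in every row and never the treatment status.
3. ITT and 'PP' differ only in rows three and four, that is, in patients with no post-baseline data. Beyond that, they can differ only in how a single missing visit is handled, since EM is described with the ITT set.
4. The contrast between the two sets is therefore one of missing-data handling and carries no information on non-adherence.

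**The visit analysed.** One definition serves both the T0–T1 and the T0–T2 analyses. A patient with T1 data only belongs to the set but has no T2 value for the T0–T2 change, which the Primary outcome measure section names as the primary parameter. The text does not say what happens to that patient in the second set.

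**Size.** The quantity that matters is the number of patients in the second row. The documents do not give it. The 80 % attendance figure is an average from an earlier trial and does not show how the missed sessions were spread over patients.

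**The case against.** The best defence has four parts.

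- *The definition is open and the set is secondary.* The label and the rule stand in the same sentence, ITT comes first, and the article never claims that the second set tests adherence. This stands as a limit on the consequences. It does not make the label right.
- *Thresholds for compliance belong in the SAP.* That would answer a complaint that no minimum is given. Here, however, the article does state a definition, and it is the wrong one for its label.
- *Any unimputed analysis must exclude a patient with full attendance and no outcome.* Correct. The exclusion of row-three patients is not a defect in itself; the defect is the retention of row-two patients under this name.
- *A treatment-based set also selects after randomisation.* Correct, and it is why such a set could only support ITT.

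Some stronger readings are tempting but not supported. A reader might infer from "including dropout due to non-compliance and loss to follow-up" in the Sample size section that the plan counts all non-compliers as dropouts and then contradicts itself. The phrase can equally mean patients who drop out because of non-compliance, and those with no later data are indeed excluded from the second set. A reader might also infer that T1-only patients will be used in the T0–T2 change. That is not stated, and a complete-case change score would drop them; the text merely leaves it open.

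**Conclusion.** The point holds as a mislabelled and loosely bounded secondary analysis set. As written, the plan would report an available-case result under the name per protocol. It rests on two things in the text: the definition has no treatment criterion, and patients may stop the intervention yet still be assessed.

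Its numerical effect cannot be given. It is tempting to build a count from the dropout rates in the Sample size section, but the 10 % and 14 % come from a group MCT study and the 20 % is this trial's planning allowance. All of them concern dropout or non-completion, and none counts assessed non-compliers. The ITT analysis and the planned 328 patients are unaffected, so the matter is one of interpretation and does not threaten the main result.

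**What to change.** 1. Rename the second set available-case. Restrict it to patients with data at the visit analysed (T1 for the T0–T1 change, T2 for the T0–T2 change) and describe it as a missing-data sensitivity analysis alongside those already listed.
2. If a per-protocol result is to be reported, define it separately and before unblinding, by a minimum number of sessions attended. The number should be the same in both arms and set by the investigators.
3. State that this set also selects on a post-randomisation variable and is supportive to ITT.

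The cost is mainly wording. Number of sessions completed is already a planned analysis variable, and the Procedure section has acceptance questionnaires for both interventions filled in after every session attended.

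Two extensions are best left out. A content rule built on the instruction that "trainers are to choose at least two units addressing cognitive biases" would need a record of units delivered to every patient, which the article does not show: adherence is rated from video of consenting patients only. It would also apply to one arm alone. A complier-average effect against an active comparator needs an exclusion restriction that is open to doubt here, and the point does not depend on it.
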